### 2.4. Intervention

Before the procedure starts, participants will be randomised in AG or in GG. Neonates in both groups will be monitored with a pulse oximeter (IntelliVue X2, Philips Medicin System, Boeblingen GmbH, Boeblingen, Germany) across the right wrist to observe heart rate and peripheral oxygen saturation during the intervention and the blood sampling. In addition, neonates in both groups will wear an eye protector (Natus Biliband Eye Protector, Natus Medical, San Carlos, California) during the treatment with laser acupuncture or oral glucose solution, following the same treatment protocol so that all participants will be manipulated equally. The eye protector will be removed 30 seconds before the heel lance.

*AG*. Participants will receive laser acupuncture at LI 4 bilaterally, 60 seconds at the left point and 60 seconds at the right point, in total 120 seconds. 30 seconds until heel lance are left.

*GG*. Neonates in this group will receive orally administered glucose solution for 30 seconds and two minutes waiting period until heel lance.

The intervention in both groups will take in total 150 seconds. Afterwards, the standardised process of blood sampling with heel lance will be carried out.

The complete procedure of blood sampling will be recorded on video, excluding the intervention with laser acupuncture or oral glucose solution. The video will start 15 seconds before heel lance and will record until blood sampling is completed. These video recordings will be analysed by a certified paediatric nurse, who will determine the PIPP for each neonate, blinded to group allocation. To improve the adherence to the study protocol a medical doctor is following written standards of procedure (SOP).

Figure 1 shows the time schedule of enrolment and assessments and Figure 2 gives information about the study course.

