### 2.5. Outcome Measurement

The primary outcome is the mean difference in PIPP score between AG and GG.

Secondary outcomes will be mean differences in heart rate change from baseline, in oxygen saturation change from baseline, and in crying time, as well as any adverse events during intervention.

Explorative outcome parameters will be general behavioural state (sleeping, awake, agitated, or crying) of the neonate before intervention, the last breastfeeding time point before intervention, and the number of heel lances performed that will be notated. The duration of blood sampling will be recorded in seconds.

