### 2.14. Data Management

Pseudonymous data will be recorded first on a Case Report Form and then on an Excel Sheet (Microsoft Excel 2010, Microsoft Corporation, Redmond, Washington, USA) for statistical analysis including data from the neonate, the mother, and the delivery, as well as information recorded during the intervention. Outcome parameters will be collected before and during intervention (e.g., heart frequency, oxygen saturation) and on the basis of video recordings of the participants (e.g., crying duration, PIPP). Adverse events will be collected and reported during the intervention and supervised by a paediatrician. However, from preliminary trials, little to no risk for adverse events is expected for the included neonates. If there will be suspicion of adverse events or harm in most cases, discontinuing or modifying allocated interventions for given trial participants will be reviewed. Furthermore, interim analyses will not be performed.

Data will be stored on restricted-access files at the Division of Neonatology, except for the study contributors.

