### 2.15. Sample Size

In a group of neonates receiving laser acupuncture, Gottschling et al. reported a pain reaction following heel lance of 6.4 ± 1.9 in PIPP score [13]. Assuming a SD (standard deviation) of 1.9 in pain scores of neonates undergoing heel lance, a sample size of 95 neonates will have a power of 80% (one-sided *t*-test) to reject the null hypothesis that the laser acupuncture and oral glucose administration are not equivalent (the difference in means, *μ*AG  −  *μ*GG, is 1.0 or farther from zero in the same direction) in favour of the alternative hypothesis that the means of the two groups are equivalent, assuming that the expected difference in means is 0. Assuming a minimal dropout of *n* = 5 neonates, we expect to include 95 participants in total.

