### 2.16. Statistical Analysis

We will compare the PIPP scores of both groups using intention-to-treat analysis (ITT). Furthermore, per-protocol (PP) analysis will be performed, since ITT analysis increases the chance of finding noninferiority (increase of type I error) [29]. Results of ITT and PP analysis will be compared.

First baseline characteristics of both groups (gestational age, sex, APGAR score, birth weight, birth size, head circumference, birth mode, and day of life at the time of heel lance) will be compared using *t*-test or Mann–Whitney *U* test for continuous variables and chi-square test or Fisher's exact test as appropriate. For differences in these characteristics, further analysis will be adjusted.

Laser acupuncture will be considered noninferior to oral glucose administration, if the upper boundary of the two-sided 95% confidence interval (CI) for the mean difference between laser acupuncture and oral glucose administration will be less than the margin, *δ* = 1. If data will not be normally distributed, nonparametric tests will be applied.

For ITT analysis, missing primary outcome measures will be imputed by using multiple imputations. For PP analysis, no imputations will be performed. Secondary outcomes will be compared using *t*-test or Mann–Whitney *U* test for continuous variables and chi-square test or Fisher's exact test as appropriate. Since interventions will be of short duration and no risks are associated with the intervention, no interim analysis will be performed.

The used statistic programs for statistical analysis will be IBM SPSS Statistics (Statistical Package for the Social Sciences) and SAS (state-of-the-art statistical analysis software).

The primary outcome measure is the PIPP score as defined above.

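### Heart-rate and oxygen-saturation changes are compared without adjusting for the baseline value; ANCOVA would be at least as precise, by an amount the protocol does not allow one to fix

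*Protocol article*

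**What the plan says.** Section 2.5 of the protocol article states: "Secondary outcomes will be mean differences in heart rate change from baseline, in oxygen saturation change from baseline, and in crying time". Section 2.16 fixes the method: "Secondary outcomes will be compared using *t*-test or Mann–Whitney *U* test for continuous variables".

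The same section has one adjustment rule. It lists "gestational age, sex, APGAR score, birth weight, birth size, head circumference, birth mode, and day of life at the time of heel lance" and continues: "For differences in these characteristics, further analysis will be adjusted". Heart rate and saturation before the procedure are not on the list.

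On what is measured, section 2.14 says: "Outcome parameters will be collected before and during intervention (e.g., heart frequency, oxygen saturation". Section 2.4 describes pulse oximetry in both arms "to observe heart rate and peripheral oxygen saturation during the intervention and the blood sampling".

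**The concern.** Subtracting the baseline is not the same as adjusting for it. A change score fixes the slope of the later value on the baseline at 1. If the true slope is different, two things follow. Part of the baseline variation stays in the outcome as noise, so the interval is wider than it need be. And if the arms differ by chance at baseline, part of that difference stays in the treatment estimate.

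The adjustment rule in 2.16 does not repair this. It acts only when a listed characteristic differs between arms, and the two relevant baselines are not listed. The article names the test itself, so this is a choice it has made, not a detail left to a fuller document.

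At stake is the precision of two secondary comparisons in a trial with about 45 evaluable neonates per arm.

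**Working it through.** **Inputs.** Total of 95 with 5 dropouts, PIPP SD 1.9, margin 1.0, expected difference 0, power 80%, one-sided test (section 2.15); 1:1 allocation (2.12). The article gives no SD, correlation or power for heart rate or saturation. Everything on those below is an assumed range.

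**The plan's own figure.** It concerns the primary outcome and serves here only to give the number per arm. Section 2.15 reads "Assuming a SD (standard deviation) of 1.9 in pain scores of neonates undergoing heel lance" and "a sample size of 95 neonates will have a power of 80% (one-sided". At one-sided 5%, n per arm = 2 × 1.9² × (1.645 + 0.842)² / 1.0² ≈ 44.7, rounded up to 45. That is 90 evaluable, plus 5 dropouts = 95, so the figure reproduces at that level.

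**Variances.** Let the baseline SD be 1, the SD during sampling k, and the correlation rho. The slope of outcome on baseline is rho × k. Up to the same factor for sample size:

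- raw change: 1 + k² − 2·rho·k
- ANCOVA: k²(1 − rho²)
- difference: (1 − rho·k)²

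The difference is a square, so in large samples ANCOVA never has the larger variance, and the two are equal only at slope 1. With k = 1 the ratio reduces to (1 + rho)/2.

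**Results.** The last column takes an effect that raw change would detect with 80% power at two-sided 5% and computes Φ((1.960 + 0.842)/√ratio − 1.960).

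| k | rho | slope | ANCOVA/change variance | 80% becomes about |
|---|---|---|---|---|
| 0.8 | 0.3 / 0.5 / 0.7 | 0.24 / 0.40 / 0.56 | 0.50 / 0.57 / 0.63 | 98% / 96% / 94% |
| 1 | 0.3 / 0.5 / 0.7 | 0.30 / 0.50 / 0.70 | 0.65 / 0.75 / 0.85 | 94% / 90% / 86% |
| 1.25 | 0.3 / 0.5 / 0.7 | 0.375 / 0.625 / 0.875 | 0.78 / 0.89 / 0.98 | 89% / 84% / 81% |
| 1.5 | 0.3 / 0.5 / 0.7 | 0.45 / 0.75 / 1.05 | 0.87 / 0.96 / 1.00 | 85% / 81% / 80% |

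For k = 1, a noncentral-t calculation with 45 per arm and one degree of freedom fewer for ANCOVA gives the same rounded powers. A simulation with 45 per arm gave variance ratios of 0.65, 0.77 and 0.88, close to the formula.

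In terms of precision, at k = 1 and rho = 0.5 the standard error falls by 1 − √0.75 = 13%, as if there were 45/0.75 = 60 per arm. At k = 1.5 and rho = 0.5 it falls by 1 − √0.964 = 2%.

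**Chance imbalance.** The raw-change estimate shifts by (slope − 1) × the baseline difference. One standard error of that difference is √(2/45) = 0.211 baseline SD. The shift is then:

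- k = 1, rho = 0.5: −0.5 × 0.211 = −0.105 SD
- k = 1.5, rho = 0.5: −0.25 × 0.211 = −0.053 SD
- k = 1.5, rho = 0.7: +0.05 × 0.211 = +0.011 SD

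**The case against.** The strongest reply is that nothing here is an error. Section 2.5 defines the outcomes as mean differences in change and 2.16 tests change. Under randomisation that comparison is valid. The outcomes are secondary, carry no stated power and no decision rule, and the noninferiority conclusion rests on PIPP alone. All of this stands and limits the weight of the point. It does not remove it, because the article fixes a method for which an alternative at least as precise is available at almost no cost.

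A reader might draw four stronger conclusions that the documents do not support.

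- *That the analysis is biased.* It is not. The imbalance effect is conditional on a chance difference and averages to zero over randomisations.
- *That about ten points of power are being lost.* This needs equal SDs and a correlation near 0.5. A painful stimulus may widen the spread, and at k = 1.5 with the same correlation the gain is about one point.
- *That a change score over-corrects whenever the correlation is below 1.* What matters is the slope. At k = 1.25 and rho = 0.8 the slope is 1 and nothing is lost; at k = 1.5 and rho = 0.7 it slightly exceeds 1 and the carry-over changes sign.
- *That these outcomes are the main independent support for the pain score.* Section 2.7 makes heart-rate and saturation change items of the PIPP, so they overlap with the primary outcome.

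A further objection concerns the covariate. The article uses the word intervention both for the 150-second treatment period (2.4) and for the heel lance (2.6 and 2.8). The pre-intervention reading in 2.14 may therefore have been taken after laser or glucose was given, and 2.4 mentions oximetry only during the treatment period and the sampling. This stands: a pre-treatment value is likely but not established. Figure 1, which was not available in the text, may settle it.

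**Conclusion.** The point holds as a minor improvement to two secondary analyses. As written, heart-rate and saturation change are compared with no adjustment for their own baselines. The comparison is unbiased, but it is less precise than ANCOVA and open to chance imbalance whenever the slope on baseline is not 1.

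The size cannot be fixed from the article. For correlations of 0.3 to 0.7, ANCOVA needs 0.65 to 0.85 of the raw-change variance if the SDs are equal, and 0.87 to 1.00 if the SD during the lance is 1.5 times baseline. The gain could thus be material or close to nil. The 80% reference power is only a yardstick. The calculation also assumes that the baseline is measured before treatment, because only then is randomisation guaranteed to balance it on average. The primary noninferiority conclusion is unaffected.

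**What to change.** In section 2.16, state that heart rate and oxygen saturation will each be analysed by ANCOVA, with the value during sampling (or the change) as outcome and treatment arm and the neonate's own baseline value of that measure as terms, whether or not the arms differ at baseline. Report the adjusted mean difference with its 95% CI. For saturation, which is bounded at 100%, use a robust or bootstrap interval. Keep the stated test for crying time, which has no baseline.

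In sections 2.5 and 2.14, define baseline as the reading taken before laser or glucose starts. If only a reading taken after treatment but before the lance exists, it may itself be affected by treatment and should not be used as this covariate.

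The cost is one or two sentences and one residual degree of freedom per model. If the pre-treatment reading is already recorded, no new data, participants or staff are needed, and the SPSS and SAS packages named in 2.16 can fit the model.

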### 2.17. Ethics and Dissemination

Participants in this trial will be protected against invasion of privacy. Therefore, the collected data and video recordings will be pseudonymous, securely stored at Division of Neonatology. This study has been approved by the Ethic Committee Graz (28-217 ex 15/16) and will be conducted with respect to the individual participants according to the Declaration of Helsinki and the Guidelines for Good Clinical Practice. The study protocol is reported in accordance with the Standard Protocol Items: Recommendations for Interventional Trials (SPIRIT Checklist 2013) [30].

The results of the present trial will be published in a peer-reviewed journal and presented at relevant conferences.

## 3. Discussion

The present observer-blinded, randomised, controlled trial has been designed to explore potential advantages of laser acupuncture in the management of neonates' pain. Due to the fact that recent evidence proved the necessity to improve healthcare and pain management in neonates, it is important to investigate new methods for pain management to provide pain associated adverse effects. Therefore, it is also important to assess pain with a validated and frequently used pain score, for example, the PIPP score, which is consistently used in clinical neonatal settings and research context providing a reliable tool for neonatal pain assessment [20–22].

In preliminary studies about acupuncture for pain relief in neonates, different results were reported. Significant pain reduction has been demonstrated in two studies, one with laser acupuncture with 30 mW at LI 4 and Shen Men and the other with light needling at Yin Tang [13, 14]. One study with acupressure showed equal pain scores and one higher pain scores in neonates treated with laser acupuncture with 10 mW at Yin Tang [15, 16]. The latest study showed significant pain reduction with NESAP combined with oral sucrose solution [17].

Due to heterogeneity across studies in regard to acupuncture modality and used acupuncture points, it is difficult to compare the results and to give clear recommendation.

We will discuss our study with the results in regard to the effectiveness of laser acupuncture and to the acupuncture LI 4 and also in regard to our control group with oral glucose solution.

One limitation of our study is the absence of a placebo control group. However, according to recent recommendations, although the placebo or sham effects of acupuncture can be estimated using experimental trials in adults, this is not the case for clinical trial with neonates suffering from pain [31].

## 4. Conclusion

Based on the heterogeneity across preliminary studies about acupuncture for pain relief in neonates, clear recommendations are missing and, therefore, it is important to add new evidence. To date, no trial has been carried out comparing laser acupuncture at LI 4 with oral glucose solution in a noninferiority setting to quantify the benefits.

Including the well-proven specificity of acupuncture at LI 4 for pain relief, we hypothesize that laser acupuncture at LI 4 will reduce pain and distress associated with minor painful procedures in healthy term neonates equally to orally administrated glucose solution.

## Figures and Tables

**Figure 1 fig1:**
[figure not shown]
Time schedule of enrolment and assessments.

**Figure 2 fig2:**
[figure not shown]
Time chart of study course. AG, acupuncture group; GG, glucose group; LI 4, Large Intestine 4; s, seconds.

## Abbreviations

AG: Acupuncture group
BW: Body weight
CI: Confidence interval
cm: Centimetre
e.g.,: Exempli gratia
GaAs: Gallium arsenide
GG: Glucose group
ITT: Intention-to-treat analysis
J: Joule
kg: Kilogram
LI 4: Intestine 4
mm: Millimetre
mL: Millilitre
mW: Milliwatt
NIPS: Neonatal Infant Pain Scale
PIPP: Premature Infantile Pain Profile
PP: Per-protocol analysis
SAS: State-of-the-art statistical analysis software
Sec: Seconds
SD: Standard deviation
SPIRIT: Standard Protocol Items: Recommendations for Interventional Trials
SPSS: Statistical Package for the Social Sciences
SOP: Standards of procedure
ST: STandards for Reporting Interventions in Clinical Trials of Acupuncture.
